[figure not shown]

- |     |                                   |
|-----|-----------------------------------|
| (a) | Glucometers, Lancets, Test strips |
| (b) |                                   |

*(Use additional sheet if necessary)*

- 8.1 List details of all specimen(s) (if any) that you may transport from Nepal in relation to your research.

- |     |              |
|-----|--------------|
| (a) | Digital Data |
| (b) |              |
| (c) |              |
| (d) |              |

|     |                                                                    |                                                                                                             |
|-----|--------------------------------------------------------------------|-------------------------------------------------------------------------------------------------------------|
| 197 | 8.2 Country of Destination:                                        |                                                                         |
| 198 | Name of Institution:                                               |                                                               |
| 199 | 8.3 Mode of Transportation of Specimen                             |                                                     |
| 200 | 8.4 How will you ensure duplicate specimens remain in the country? |                                                                                                             |
| 201 |                                                                    |  |
| 202 | (If necessary use additional sheet)                                |                                                                                                             |
| 203 |                                                                    |                                                                                         |
| 204 | 9. Is this research part of your Thesis?                           |                                                                                                             |
| 205 | Yes            | No                                                                                  |
| 206 | If yes,                                                            |                                                                                                             |
| 207 | For what degree and in which subject?                              |                                                            |
| 208 | From which university?                                             |                                                               |
| 209 | From which country?                                                |                                                                         |

## Part – II

### Financial Information

#### 10. Research Title:

Community Based Management of Diabetes in Nepal: Study Protocol for a Cluster-Randomized Controlled Trial

#### 11. Name of the funding organization:

Partial funding from Aarhus University. The project implementation funds are sought from other donors.

## Part – III

### Research Proposal Description

#### 12. Research Title:

Community Based Management of Diabetes in Nepal: Study Protocol for a Cluster-Randomized Controlled Trial

#### 13. Proposal Summary (maximum 500 words):

**Background:** Type 2 diabetes is one of the fastest growing chronic diseases worldwide. Despite its growing burden there is a lack of population approaches to reducing blood sugar among persons with diabetes, especially in developing countries. The health complications associated with type 2 diabetes can be prevented, delayed, or improved via early diagnosis and effective management. This research aims to examine the impact of a family-based home health education intervention on type 2 diabetes provided by Female Community Health Volunteers (FCHVs) at Lekhnath Municipality of Nepal.

**Method/design:** This is a community-based, open-masked, two-armed, cluster-randomized controlled trial with 7 randomly selected intervention and 7 wait-list control sites in Lekhnath Municipality of Nepal. A total of 112 subjects with type 2 diabetes will be recruited from the intervention sites and 112 subjects from the wait-list control sites. A 12-month family-based life style intervention will be administered through the help of FCHVs based on the Health Belief Model framework. Wards in the wait-list control will continue to manage their poor glycemic condition as usual and their intervention will be delayed for 12 months. Participants will be measured at baseline and 12 months later. The primary outcome is measures of glycemic control mean fasting blood glucose levels. Secondary outcome measures of the study include body mass index, blood pressure, alcohol use, tobacco use, diet intake, knowledge, quality of life, depression scores, physical activity, social support, and sedentary behaviors.

**Discussion:** The perspective of this study is to develop and implement, in collaboration with the community people, community-based, culturally sensitive diabetes prevention and control programs. Monitoring blood glucose with point-of-care testing at home can diagnose as well as monitor how well diabetes is controlled. Moreover, our study will add to the existing global evidence on models involving lay health workers in the mitigation of the growing burden of non-communicable diseases particularly related to diabetes. If the health promotion package is found to be effective, the approach can be easily adopted into the existing primary health care delivery system of Nepal. It is furthermore anticipated that the model may also serve as an affordable tool for evidence-based integrated care for improvement of diabetes management in other developing countries.

## 14. Introduction:

### 14.1 Background of Study (maximum 500 words):

While communicable diseases remain an important public health issue in developing countries, the rising burden of non-communicable diseases and their risk factors are rapidly rising too, posing a double burden on health systems. Diabetes is increasingly becoming a significant public health problem worldwide, leading to high morbidity and mortality resulting from clinically severe complications. The global prevalence of diabetes in 2010 was estimated to be around 6.4%, affecting 285 million adults, and is expected to increase to 7.7% by 2030. With ageing, the prevalence of diabetes is expected to increase by 69% in low-and middle-income countries (1). In particular, type 2 diabetes is becoming more widespread globally, accounting for over 90% of all diabetes cases (2). The rising prevalence is attributed to various modifiable risk factors such as changes in nutrition and life styles leading to physical inactivity and obesity as well as non-modifiable risk factors including family history and age related factors (3). Type 2 diabetes has reached epidemic proportions in South-East Asia Region, leading to significant increases in morbidity and mortality in recent years(4). Indeed, we noted in our previous systematic review and meta-analysis that type 2 diabetes is emerging as a major health care problem in Nepal, with a prevalence rate of 8.4% (5). There is also paucity of data on type 2 diabetes prevalence and available studies are not consistent with in their data collection methods regarding type 2 diabetes and related modifiable risk factors (6). Hence a study of such nature will help us to understand the problem and to design an appropriate intervention for diabetes management at the community level.

### 14.2 Statement of the Problem and Rationale / Justification (maximum 500 words)

Population-based approaches that reduce the population level of blood glucose by a small amount or that prevent the increase in blood glucose with age can lead to marked reduction in the risk of type 2 diabetes (7). It has been shown that application of population-based interventions to target modifiable preventable risk factors could prevent at least 80% of non-communicable diseases, including type 2 diabetes (8). A number of recent studies offer scientific evidence for reducing the epidemic of type 2 diabetes through support for lifestyle modification(9,10). However, to date prevention programs in low-and middle-income countries have only had a modest effect on reducing diabetes through primary prevention(11) and the best approach to reduce blood glucose level is still unclear. A study by Ramchandran and colleagues in India reported that lifestyle intervention programs followed by advice from a health care advice exhibit a latent potential towards improving health outcomes in adults living with diabetes. The intervention improved glycemic level in diabetics, with an estimated 0.1% reduction in their glycosylated hemoglobin values in the treatment group (12). However, since the intervention was only targeted at middle-class working people, the findings would be difficult to extend to community level. In another intervention by Balagopal and colleagues in India, a significant reduction in blood glucose level was observed among the participants. Unfortunately, the study did not include a control group and lacked details

about the nature of community health workers(13). This reflects the need for more operational research in community health worker population approaches to reducing blood sugar among persons with type 2 diabetes.

248

249

250

251

252

253

254

255

256

257

258

259

260

261

262

263

264

265

266

267

268

269

270

271

14.3 Conceptual framework

[figure not shown]

## 14.4 Research Objectives / purpose / aim of the study:

### General

To explore the potential role of female community health volunteers for diabetes management at Lekhnath Municipality of Nepal

### Specific

To evaluate the effect of a family-based home health educational intervention administered by female community health volunteers on reduction of blood glucose levels among diabetes individuals

## 15. Research Design and Methodology

### Research Method

Qualitative ☐ Quantitative ☒ Combined ☐

### Study Variables:

Primary outcome: Measures of glycemic control (Mean fasting blood glucose levels)

Secondary outcomes: Body Mass Index, blood pressure, alcohol use, tobacco use, diet intake, knowledge, quality of life, depression scores, physical activity, social support, and sedentary behaviors.

### Type of Study (Specify):

Community-based cluster-randomized controlled trial

### Study Site and Its Justification:

The study will take place in the Lekhnath Municipality, a semi-urban area of the Western Region of Nepal (Figure 1). The municipality has a total population of 58,816 in the census carried out in 2011 with 14,937 households and is administratively divided into 15 smaller units called *wards*. Each ward will be considered as 1 cluster. The municipality has a literacy rate of 85%, life expectancy of 59.7 years, and sex distribution of 31,951 females and 26,865 males(14). According to the Kaski District Public Health Office, there were 123 FCHVs in the municipality in 2013. No previous population-based interventions for diabetes at the population level have been carried out in the past. The epidemiological transition in the Western Region is more advanced than elsewhere in Nepal; indeed, it has the highest proportion of those with severe major risk factors for non-communicable diseases(15).

292  
293  
294  
295  
296  
297  
298  
299  
300  
301  
302  
303  
304  
305  
306  
307  
308  
309  
310  
311  
312  
313  
314  
315

**Study Population (Specify):**

The study population is diabetes patients who will be identified by screening.

**Study Unit:**

Wards (Clusters)

316

## Sampling Methods / Techniques (Specify)

The COBIN project has a population framework of all eligible participants prepared from the Voter List of the Election Commission. A systematic random sampling will be conducted to select participants in the baseline survey. If there is more than one participant from the same household eligible to participate in the study at the time of data collection, the *Kish* method will be adopted to select the participant. The same method will be applied for recruiting participants in the intervention phase.

The Lekhnath Municipality has 15 administrative units called wards (clusters). Out of 15 such wards, 1 ward was excluded by using simple random sampling before the randomization. Randomization was done for the clusters dividing 7 as intervention and 7 as control. After that, respondents who participated in the baseline survey will be the participants of the study.

Data will be collected by specially trained research assistants with a health professional background. Data about sociodemographic factors, lifestyle and prior illness will be collected by interviewing participants using STEPS questionnaires. Anthropometric data (weight, height, waist circumference) and blood pressure will be measured by the trained research assistants with a health professional background, height by a flexible non-stretchable measuring tape, weight by digital weighing machine, waist circumference by centimeter scale and blood pressure by digital sphygmomanometer.

Fasting blood glucose for the participants will be estimated by using a standardized digital glucometer (Infopia Co., Korea), using the capillary finger prick method. On a pre-informed date, fasting blood glucose estimation will be done. (Fasting being defined as no caloric intake for at least eight hours). Participants will be reminded by telephone for fasting glucose testing a day before the test. A person will be considered to be having diabetes if he/she will have fasting capillary blood glucose  $\geq 7.0$  mmol/l.

The baseline survey will be performed in both the intervention and wait-list control clusters. The survey tool will be adopted from the WHO STEPWISE Package, which includes physical measurement (height, weight), socio-demographic information (age, sex, family size, occupation, income, and education), and life style factors (current exposure to tobacco and alcohol, diet and physical activity). Participants will be asked to provide a written consent to have measured via a finger stick blood sample and Glucometer. The record of FCHV visit will be maintained by a supervisor. The same methodology will be used to conduct the follow-up survey after one year in both intervention and wait-list control clusters. Knowledge and skills of FCHVs will also be assessed.

317

318

A 12-month family-based life style intervention will be administered through the help of FCHVs. The framework will be based on the Health Belief Model. According to this model, the life style intervention program will include objectives based on individual perceptions (perceived susceptibility, perceived severity) and likelihood of action (perceived benefits, perceived barriers, cues to action and self-efficacy) of diabetes prevention. The intervention component will be developed by a panel consisting of health education experts, diabetologists, health workers and a diabetes patient. FCHVs will receive a seven-day training package after randomization highlighting: a) Introduction to the non-communicable diseases/diabetes; b) identifying populations at risk using a checklist including physical inactivity, family history, smoking and tobacco use, and alcohol consumption; c) screening techniques of blood glucose level, body mass index, blood pressure, and other cardio-vascular diseases (CVDs), as well as referral for those who have poor glycemic scores; d) providing health education (type 2 diabetes, CVDs, their risk factors, meal planning, exercise training activity, maintaining or reducing body weight, smoking cessation and personal hygiene; e) recording, reporting and follow-up. Training materials will be developed by involving local major stakeholders. The developed materials will be pretested with the FCHVs of the Lekhnath Municipality. On average, one volunteer will have to visit 25 households 3 times a year and provide counseling and measure blood glucose levels of selected respondents. FCHVs will also receive health education materials (poster, pamphlet), test strips, glucometers, tape, digital sphygmomanometer, and a recording register during training sessions.

The intervention to wards in the wait-list control will be delayed for 12 months. The participants allocated to the control group will be put on a waiting list and offered to participate in the intervention only after completion of the 12 months' assessment of the intervention group.

The same methodology will be used to conduct the follow-up survey after one year in both the intervention and wait-list control clusters. i.e., a follow-up survey will be carried out through trained professional health workers such as nurses and health assistants.

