## Part – IV

### Ethical Consideration

22. Regarding the human participants:

Are human participants required in this research? If yes, provide justification.

☒

Yes (*provide justification*)

☐

No

How many participants are required for the research? Explain.

2643

What is the frequency of the participant's involvement in the research? Explain.

2

Clearly indicate the participant's responsibilities in the research. What is expected of the research participants during the research?

Participants will provide information and receive health information package in intervention VDCs

Are vulnerable members of the population required for this research? If yes, provide justification.

No

Are there any risks involved for the participants? If yes, identify clearly what are the expected risks for the human participants in the research and provide a justification for these risks.

No

Are there any benefits involved for the participants? If yes, identify clearly what are the expected benefits for the participants.

For the participants in the intervention VDCs, they will get an opportunity to measure their blood glucose level, blood pressure and receive health education package from FCHVs.

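### Diabetes is defined by one finger-prick reading of 7.0 mmol/L or more, so known patients below it drop out of the survey prevalence and the trial population is broader and narrower than the type 2 diabetes label it carries

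*Protocol*

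**What the plan says.** All references are to the Protocol.

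- **Case rule** (Sampling Methods / Techniques): "A person will be considered to be having diabetes if he/she will have fasting capillary blood glucose" at or above 7.0 mmol/L.
- **Measurement** (same section): "On a pre-informed date, fasting blood glucose estimation will be done", with a glucometer, "using the capillary finger prick method". Fasting means at least eight hours without calories, and participants get a telephone reminder the day before. No repeat reading is described.
- **History** (same section): "Data about sociodemographic factors, lifestyle and prior illness will be collected by interviewing participants using STEPS questionnaires". Nothing links the answer to diabetes status or to entry.
- **Contacts** (Ethical Consideration): the form asks "What is the frequency of the participant's involvement in the research? Explain" and the entry is 2. That fits baseline plus 12 months and shows no confirmatory visit.
- **Population labels**: the Study Population entry reads "The study population is diabetes patients who will be identified by screening". The Proposal Summary reads "A total of 112 subjects with type 2 diabetes will be recruited from the intervention sites", with 112 more from the control sites. The second sample size calculation is headed as being for diabetic populations.
- **Survey size** (Sample size): 2643, based on an expected diabetes prevalence of 9.5%.

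**The concern.** The reading alone decides diabetes status, so the rule and the labels describe different groups of people.

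In the survey, someone with an established diagnosis whose glucose is held below 7.0 by treatment is not counted. The resulting figure is the prevalence of a reading of 7.0 or more. It would be reported as the prevalence of diabetes.

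In the trial, the enrolled group leaves out controlled patients and takes in anyone with one high reading, whatever their history. A conclusion about managing type 2 diabetes would then be drawn from a group defined differently. The information needed to tell readers who was enrolled may already be in the interview, but the rule does not use it.

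**Working it through.** **1. Apply the rule as a field team would.**

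| Reported history | Reading (mmol/L) | Counted in survey prevalence | Can enter trial |
|---|---|---|---|
| Known, on treatment | 6.5 | No | No |
| Known, on treatment | 7.1 | Yes | Yes |
| None | 7.1 on the day, usual level below 7.0 | Yes | Yes |
| None | 6.5 | No | No |

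Row 1 is a diabetes patient whom the prevalence omits. Row 3 is called type 2 diabetes on one reading.

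**2. Reproduce the plan's figures.**

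- Survey: 1.96² × 0.095 × 0.905 / 0.05² = 132.1. Multiplying by design effect 2 and 8 strata and dividing by response 0.8 gives 2642.3, rounded up to 2643.
- Trial: a difference of 1 with SD 2.1, two-sided 5% and 80% power needs 70 per arm. 70 × 1.1 = 77 = 7 × 11. Then 11 / 0.7 = 15.7, rounded up to 16, and 7 × 16 = 112 per arm, or 224 in total.

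Both reproduce. The point concerns a definition; no stated figure is wrong.

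**3. Size of the omission from prevalence.** The Protocol does not say how many people have a known diagnosis and a reading below 7.0. Suppose a share m of all people with diabetes do (an assumption), and true prevalence is 9.5%. The rule then counts 9.5% × (1 − m) of the population as true cases: 8.55% at m = 10%, 7.6% at m = 20% and 6.65% at m = 30%. One-off high readings push the other way, so the net direction is unknown.

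**4. Who enters the trial on a single reading.** The Protocol gives no meter or day-to-day error, so this is illustrative. Assumptions:

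- Non-diabetic usual glucose is normal with mean 5.3 and SD 0.55.
- Diabetic usual glucose is 6.5 plus a gamma variable (shape 1.5, scale 1.6).
- Reading = usual value × (1 + CV × a standard normal draw).
- The mixture is set so that 9.5% of readings reach 7.0, with 2,000,000 simulated people per CV.

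| Total CV | Enrolled with usual level below 7.0 | Of 224 | Enrolled from the non-diabetic component | Of 224 |
|---|---|---|---|---|
| 6% | about 8% | 18 | about 5% | 11 |
| 8% | about 13% | 30 | about 10% | 22 |
| 10% | about 20% | 46 | about 17% | 38 |
| 12% | about 30% | 67 | about 27% | 60 |

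Counts use unrounded shares. About 4 percentage points of the third-column share at every CV come from the modelled diabetic component, which starts at 6.5. These are people with diabetes whose usual level is between 6.5 and 7.0, not people without it. The last pair of columns takes everyone enrolled from the non-diabetic component, including the few whose usual level is 7.0 or more.

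A second model has prevalence 5% to 9.5%, non-diabetic mean 5.2 and SD 0.5 to 0.6, CV 6% to 15%, and a diabetic component that starts at 7.0. It puts the share with a usual level below 7.0 at about 2% to 48%. The spread shows how far the figure depends on what is assumed.

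**The case against.** **The text says if, not only if.** Exclusion of everyone below 7.0 is therefore an inference. It is a fair one: no other route to being classed as diabetic appears in the Protocol, and the population is defined as those found by screening. If known patients were meant to count, the Protocol needs to say so.

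**Selecting on glucose suits a glucose-lowering trial.** The specific objective is to reduce blood glucose, and the summary describes control wards as having poor glycaemic control. Admitting well-controlled patients would add people with little room to improve. This stands, and the entry rule is not challenged here.

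**Prevalence is not a listed objective.** True of the research objectives. It is nevertheless the quantity on which the survey is sized.

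**The eight-hour fast and the reminder reduce false high readings.** They do, but they do not remove day-to-day or meter variation.

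Three stronger readings may tempt a reader and are not supported:

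- *The treatment comparison is biased.* The same rule and measurement method apply in both arms, so regression to the mean is expected in both. It affects change within an arm but does not by itself bias the difference between arms.
- *The trial loses a known amount of power.* If a share f of participants gained no effect at all, power would be Φ((1 − f) / (2.1 × √(2/70)) − 1.96): 80.4% at f = 0, 71.8% at 10%, 61.6% at 20% and 50.5% at 30%. Both f and the zero response are assumptions, and people with lower usual glucose may respond partly.
- *Splitting by known and newly detected status isolates the one-off high readings.* It does not. A treated patient whose usual level is 6.5 can read 7.1 on the day and enter as a known case.

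**Conclusion.** The point holds as a mismatch between the case rule and what the survey and trial are said to describe. As written, known or treated patients reading below 7.0 are missing from the survey's diabetes prevalence. The trial population is people with one screening reading of 7.0 or more, and the labels in the Proposal Summary and the Study Population entry claim something else.

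The number of patients missed cannot be derived from the Protocol, nor can the share enrolled whose usual level is below 7.0. The 8% to 30% range rests wholly on the assumed distributions and a total CV of 6% to 12%, and should be cited only with those assumptions. What is at stake is the meaning of the prevalence figure and the population to which the result applies. The validity of the comparison between arms is not in question on this ground.

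**What to change.** 1. **Survey.** For classification and prevalence, count a reading of 7.0 mmol/L or more, or a previous diagnosis or current glucose-lowering treatment reported at interview. The Protocol mentions prior illness but does not reproduce the questionnaire, so check that both items are asked explicitly.
2. **Trial population.** Reconcile the Proposal Summary, the Study Population entry and the diabetic sample size section with the rule in the sampling section. Describe participants as people with a screening fasting capillary reading of 7.0 mmol/L or more.
3. **Known versus newly detected.** Record this for every participant to describe who was enrolled. Any result by this status is descriptive only: one-off high readings can occur in both groups, and about 77 analysed per arm leaves small subgroups.

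The threshold and the entry rule are not altered, so dilution from one-off high readings is not removed.

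**Cost.** Protocol wording and an interview item, with no extra blood test and no change in sample size. The stated population becomes narrower than type 2 diabetes. The survey definition will also differ from the trial entry rule, and each must be labelled as such wherever it is reported.

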## Potential Biases (if applicable):

There may be possibility of a selection bias in this study due to high loss to follow-up or failure to use intention to treat analysis. Moreover, selection bias can also be introduced through participant recruitment as our study will recruit participants after the clusters have been randomly allocated.

In the same way recruitment bias could occur in this study due to poor allocation concealment. If the allocation could not be concealed from the people doing the recruiting, there may be danger of recruitment bias.

Another important bias that could occur is the contamination bias. For instance, the subjects in the control group can be inadvertently exposed to the intervention group.

However, the risk of contamination will be minimized by randomization at the level of clusters. In order to reduce the possibility of contamination, we also have plans to collect every possible means of contamination between intervention and wait-list control participants during the follow-up survey, and, if these are found to be significant, we will make adjustments while estimating the effect.

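### Nothing keeps the 12-month assessors unaware of ward allocation, and contamination questions sit in the same survey that records the outcomes, so avoidable assessment bias is possible, mainly in the self-reported secondary outcomes

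*Protocol*

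**What the plan says.** **Masking.** Protocol section 13 (Proposal Summary) calls the trial a "community-based, open-masked, two-armed, cluster-randomized controlled trial". The term is not explained, and no section says who, if anyone, is masked.

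**Allocation.** Section 15 (Study Site and Its Justification) makes each ward one cluster. Sampling Methods / Techniques reports the randomization of seven wards to each arm as already done.

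**Follow-up assessment.** Sampling Methods / Techniques says that "a follow-up survey will be carried out through trained professional health workers such as nurses and health assistants". It also says: "The same methodology will be used to conduct the follow-up survey after one year in both intervention and wait-list control clusters". The baseline method is an interview with physical measurements: "Data about sociodemographic factors, lifestyle and prior illness will be collected by interviewing participants using STEPS questionnaires". Fasting glucose is measured "using a standardized digital glucometer (Infopia Co., Korea), using the capillary finger prick method", and blood pressure with a digital device.

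**Contamination questions.** Potential Biases says that the team plans to "collect every possible means of contamination between intervention and wait-list control participants during the follow-up survey".

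**Outcomes.** Study Variables names mean fasting glucose as primary. Besides body mass index and blood pressure, the secondary outcomes are "alcohol use, tobacco use, diet intake, knowledge, quality of life, depression scores, physical activity, social support, and sedentary behaviors".

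**The concern.** Arm is a property of the place, so anyone who knows the ward list knows the arm of every participant visited there. An assessor who does not know the list can still learn the arm from answers about contact with the volunteers. An interviewer who knows the arm may probe, prompt or code answers differently without meaning to.

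At stake is the reading of the secondary results. A difference in reported diet, activity or smoking could be partly a difference in how the questions were asked. The random-effects model in section 17 handles correlation within wards. It cannot separate an assessor effect that runs along with arm from an intervention effect, and a larger sample would not shrink that effect. The likely direction favours the intervention, but this is not certain.

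This cannot be left to a statistical analysis plan: who knows the allocation and when each item is asked are field procedures, settled before the data exist.

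**Working it through.** The point rests on text, so the relevant sections are set side by side first.

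| Question | What the protocol gives | Where |
|---|---|---|
| Is anyone masked? | Open trial; no masked assessor described | Section 13 |
| Does the location reveal the arm? | Yes, to anyone who knows the list: ward = cluster, allocation already done | Section 15, Study Site; Sampling Methods |
| Who assesses at 12 months? | Nurses and health assistants, in person | Section 15, Sampling Methods |
| Are exposure questions kept apart from outcomes? | Same survey; no order and no separate staff stated | Section 15, Potential Biases |
| Is the risk acknowledged? | Selection, recruitment and contamination bias are listed; assessment bias is not | Section 15, Potential Biases |
| Are field work and analysis separated? | The PhD student is to collect primary data and perform the analysis | Section 16 |

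Potential Biases already recognises the mechanism for another group: it warns of bias if the people who recruit know the allocation. The same reasoning is not carried to the people who measure the outcomes.

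**Which outcomes are exposed.** There are eleven secondary outcomes.
- Two are physical measurements: body mass index and blood pressure.
- Five are behaviours: alcohol, tobacco, diet, physical activity and sedentary behaviour. Lifestyle data are documented as taken by interview. The volunteers' listed teaching topics include meal planning, exercise and smoking cessation; alcohol appears only in the risk checklist.
- Four are neither: knowledge, quality of life, depression and social support. Their mode of administration is not stated; they probably rest on the respondent's answers.

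Check: 2 + 5 + 4 = 11.

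**A yardstick for the primary outcome (not an estimate).** The planned size reproduces from section 15, Sample size (difference 1 mmol/L, SD 2.1, 80% power, intraclass correlation 0.01, dropout 30%) and section 17 (two-sided 5%):
- n per arm before clustering = 2 × [2.1 × (1.960 + 0.842) / 1]² = 69.2, so 70.
- Design effect = 1 + (11 − 1) × 0.01 = 1.10; 70 × 1.10 = 77 = 7 × 11.
- 11 / 0.70 = 15.7, so 16 per ward; 7 × 16 = 112 per arm, 224 in total.

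Nothing in this point changes that size. The standard error of the difference is 2.1 × √(2 × 1.1 / 77) = 0.355 mmol/L. For an assumed arm-related measurement bias b, the chance of a false positive is Φ(b/0.355 − 1.96) + Φ(−b/0.355 − 1.96):

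| Assumed b (mmol/L) | Two-sided type I error |
|---|---|
| 0 | 5% |
| 0.1 | 5.9% |
| 0.2 | 8.7% |
| 0.3 | 13.5% |
| 0.5 | 29.1% |

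The values of b are assumptions. The protocol gives no basis for choosing among them, and a device reading makes a value near zero plausible.

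**The case against.** Much can be said for the plan. Delivery and assessment are already separated: the volunteers give the intervention, while nurses and health assistants do the follow-up survey. One method, including one definition of fasting, applies in both arms. An open trial of home education is legitimate, and participants will colour their own answers whatever the assessor knows. These points stand and limit the concern, but they do not meet it: staff who did not deliver the intervention may still know which wards received it.

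Some stronger readings do not stand.

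- *Assessors will learn the arm before they record outcomes.* A reader might infer this from the contamination questions. The protocol fixes no order and does not say who asks them. Glucose is taken on a date notified in advance, which may differ from the interview date. The questionnaires were to be annexed and are not shown. Only the possibility is established.
- *The glucose result is biased by rescheduling or repeat finger pricks.* The protocol mentions neither. What it gives is a digital meter, an eight-hour fast and a telephone reminder the day before. Any mmol/L figure built on differential fasting would need an assumed excess of non-fasting readings and an assumed rise per reading, neither of which is in the document. The lack of a detailed rule on rescheduling or on which reading counts is missing detail, not a fault.
- *Nine of the eleven secondary outcomes are self-reports of behaviours the volunteers teach.* At most five are behaviours, and not all of these are listed teaching topics.

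**Conclusion.** The concern holds as a weakness in field design that is cheap to correct. The trial is open, allocation follows the ward, outcomes are taken in person, and contamination questions sit in the same survey; nothing keeps assessors unaware of allocation. They can therefore know or learn the arm before recording outcomes, and the protocol does not acknowledge the resulting bias.

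The risk is greatest for the interview-based secondary outcomes. It is smaller for fasting glucose and blood pressure. Its size cannot be derived from the document for any outcome. The conclusion assumes that a procedure not described is not planned, and that the four outcomes with no stated mode of administration are respondent-reported. It does not show that the primary comparison is biased.

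**What to change.** With the staff already planned:

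1. Do not tell follow-up assessors the ward allocation, and state in section 13 who is and is not masked.
2. Schedule each assessor across both intervention and control wards, so that assessor and arm are not tied together.
3. Record glucose, physical measurements and self-reported outcomes before any question on volunteer contact or contamination.
4. Add assessment bias to Potential Biases.
5. Report the self-reported secondary outcomes as unmasked.

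The cost is a rota, a fixed questionnaire order and some extra travel between wards. Sample size and analysis do not change. Masking will be imperfect, because participants know what they received and may say so; item 5 is needed for that reason even if items 1 to 3 are followed.
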